### Criteria for discontinuing or modifying allocated interventions {11b}

Participants will be allowed to leave the study at any time for any reason if they wish to, without any consequences. Participation in this study will also be ended by the investigator if the participant is uncooperative and/or does not attend study visits. This study will be prematurely ended in case of any adverse events or procedural-related complications or if the independent specialist in acupuncture and moxibustion advises its termination. The criteria for study termination will also include any serious adverse event (SAE).

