### Trial design {8}

This will be a single-center, single-blind, parallel-arm, randomized clinical trial. Forty-two healthy male volunteers will be allocated into the AE group, NAE group, or blank group with an allocation ratio of 1:1:1. This trial will comprise 1-week baseline (baseline sleep), 1-week preventative treatment, 30-h TSD, and 24-h after waking follow-up periods. Figure 1 shows the flow diagram of the trial.

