#### Blank control group

Participants in the blank control group will not be given any treatment.

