### Sleep deprivation procedures

The SD trial will be performed at the Clinical Centre for Acupuncture and Moxibustion at the First Affiliated Hospital of Changchun University of Chinese Medicine, China. Sleep deprivation will start at 7:00 am (baseline). Total sleep deprivation will be 30 h. During their free time, participants will spend most of their time in a large common room with both natural and electric lighting. During SD, participants will be permitted to play games, read, review school work, and use their personal electronic devices for entertainment. They will also be allowed to freely interact with each other and with the research staff. Napping, caffeinated beverages, and strenuous physical activity will be prohibited. Participants will be served breakfast, lunch, and dinner in the hospital cafeteria, with free access to snacks during their free time in the common room. Throughout the trial, participants will be constantly supervised by the researcher to ensure they do not fall asleep.

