## Statistical methods

### Statistical methods for primary and secondary outcomes {20a}

Descriptive statistics will be used to describe the study population. Comparisons of the study groups by age, gender, and outcome characteristics will be done using analysis of variance (ANOVA) or chi-square tests. Depending on whether the data are normally distributed, the continuous variables will be described as the mean (standard deviation) or the median. One-way analysis of variance (ANOVA) will be used for comparisons among the three groups. Continuous variables, including the POMS scores, PANAS scores, and FaceReader, will be compared among the three groups at all time points using ANOVA. The Student-Newman-Keuls method will be used for pairwise comparisons. Adverse events will be summarized for each group and compared using Fisher’s exact tests. Statistical analyses will be performed using SAS 9.1.3. Statistical significance will be set at *p* ≤ 0.05.

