#### Adverse event reporting and harms {22}

Any adverse events reported by the participants will be recorded in the CRF, including the time, symptoms, signs, degree, duration, laboratory test index, treatment and outcome, follow-up, and follow-up time. Common treatment-related adverse events to be tested will include subcutaneous hematoma, continuous post-needling pain, itching at the sites of the needle insertion, and dizziness.

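### The discontinuation section, as worded, ends the whole study on any adverse event, which contradicts the rest of the protocol's plans for adverse events

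*Protocol article*

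**What the plan says.** Section {11b} of the protocol article opens with two rules about individuals: a participant may leave at any time, and the investigator may end the participation of someone who does not cooperate or does not attend. The third sentence changes subject: "This study will be prematurely ended in case of any adverse events or procedural-related complications". It adds a further route, namely advice to terminate from an independent acupuncture and moxibustion specialist. The fourth sentence reads: "The criteria for study termination will also include any serious adverse event (SAE".

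Four other places bear on the point:

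- Adverse event reporting and harms {22}: "Any adverse events reported by the participants will be recorded in the CRF", with details that include treatment, outcome and follow-up. It continues: "Common treatment-related adverse events to be tested will include subcutaneous hematoma, continuous post-needling pain", and also names itching and dizziness.
- Statistical methods for primary and secondary outcomes {20a}: "Adverse events will be summarized for each group and compared using" Fisher's exact tests.
- Procedure for unblinding if needed {17b}: a participant with a serious adverse event may be unblinded before the trial ends so that prompt treatment can be given, with a report form and a note on the case report form.
- Trial design {8}: "Forty-two healthy male volunteers will be allocated into the AE group, NAE group, or blank group", in the ratio 1:1:1. Of the blank control group the article says: "Participants in the blank control group will not be given any treatment".

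**The concern.** A study-level stopping rule should say which events stop the study. This one says that any of them do. If it is followed, a minor and expected needling reaction in one participant closes a trial that has the safety of electroacupuncture among its stated objectives. If it is not followed, the trial departs from its published protocol at the first minor event. Investigators, the ethics committee that monitors the trial and later readers then cannot tell from the article which rule was in force.

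**Working it through.** **Which level the sentence works at.** The sentence before it ends a person's participation; this one ends the study. It goes on to speak of the study's termination, and the next sentence adds serious events as a further criterion for terminating the study. The word also in that sentence treats what came before as a study-termination criterion. The study-level reading is therefore the natural one.

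**The rule set against the other sections.**

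- {22} expects four kinds of needling event, calls them common, and has each reported event recorded through to outcome and follow-up. This presupposes that the trial continues after one occurs.
- {20a} compares adverse events across groups. If the trial stopped at a single event, that event would fall in one of three groups of 14. The three possible tables each have probability 14/42 = 1/3, so Fisher's exact test gives p = 1 whichever group it falls in. The planned comparison would have no content.
- {17b} handles even a serious event as a matter for one participant while the trial is still open.
- Within {11b}, a serious adverse event is already an adverse event, so the fourth sentence adds nothing if the third means what it says.

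**How often a literal rule would be triggered.** The plan states no figure to reproduce, and it gives no event rate, so the risks below are assumptions.

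- Participants needled: 42 at 1:1:1 is 14 per group; two needled groups give n = 28.
- Formula: the probability of at least one event is 1 − (1 − p)^n, with participants treated as independent and p the risk per participant over the trial.

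| Assumed p | n = 28 (needled only) | n = 42 (all) |
|---|---|---|
| 1% | 1 − 0.99^28 = 0.245 | 1 − 0.99^42 = 0.344 |
| 5% | 1 − 0.95^28 = 0.762 | 1 − 0.95^42 = 0.884 |
| 10% | 1 − 0.90^28 = 0.948 | 1 − 0.90^42 = 0.988 |

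The right-hand column is shown because the trigger is not confined to needling and every participant undergoes sleep deprivation (Sleep deprivation procedures: "Total sleep deprivation will be 30 h"). The needled-only column is the more cautious one and is used in the conclusion.

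**The case against.** The strongest reply is that nobody meant this. The section heading concerns allocated interventions, the two preceding sentences concern individuals, and the serious-event criterion makes sense only if something narrower was intended. The rest of the article assumes that the trial carries on after an event, so it is unlikely that anyone would have closed it for a bruise. On this view it is a wording error that leaves the primary outcome, the analysis, the power and the error rate untouched. The probabilities quantify a rule that was probably never intended, and they rest wholly on assumed rates.

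Much of that stands. A drafting slip is the likeliest explanation, and the figures only illustrate what the literal text would do. Nor is it right to say that the article offers no route for non-serious events: the same sentence allows the specialist to advise termination, and {22} says how each event is documented. The article condenses a fuller protocol, so the absence of severity grading is no finding.

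What remains is that the article does not merely omit a rule. It states one, and the stated rule gives the wrong result. A slip in a stopping rule leaves the reader to guess the intended rule.

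Two stronger readings are tempting. A reader might infer that the trial was, or was bound to be, stopped early and its efficacy answer lost. The documents do not support this: they report no event and no stop, and the chance of triggering the rule is not the chance of losing the efficacy result, which also depends on how many participants had finished by then. A reader might also infer a deliberate design decision that makes the trial unworkable. The inconsistency with {22}, {20a} and {17b} points the other way.

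**Conclusion.** The point holds as an error in a stated decision rule: read as written, {11b} terminates the study on any adverse event or procedural complication, against three other sections and the sentence that follows it. This conclusion needs no event rate, because {22} itself calls the listed reactions common. For scale, at an assumed 1% to 10% risk per needled participant, with 28 independent participants, a literal rule would be triggered with probability 25% to 95%, and 76% at 5%. The wording should be corrected; the finding does not show a flaw in the efficacy comparison.

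**What to change.** In the third sentence of {11b}, remove adverse events and procedural complications as a trigger for ending the study. State that non-serious events are recorded and followed up as in {22}, and may lead to stopping the individual's treatment.

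Make study-level termination depend on the independent specialist's advice after review of any serious adverse event, at least those judged related. Merely keeping the present fourth sentence would not be enough: one unrelated serious event, even in an untreated control participant, would still end the study automatically, and that fits poorly with {17b}.

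Trial status gives 20 May 2021 as the end of recruitment, so the trial may already be finished. In that case, state in the results report which stopping rule was applied.

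The cost is a wording amendment and ethics notification, or one sentence in the report. No participants, procedures or analyses are added.

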### Strategies to improve adherence to interventions {11c}

All acupuncture treatments and laboratory tests will be provided for free to improve adherence to the intervention protocol. All subjects will be required to sign a written informed consent before participating and will be compensated monetarily. Participant and acupuncturist signatures will be required after each acupuncture session to monitor adherence.

### Relevant concomitant care permitted or prohibited during the trial {11d}

To ensure that participants within the three groups get adequate sleep (at least 7 h per night for a week before the first clinical trial) during the sleep baseline period, we will use sleep logs and actigraph (an automatic-scoring actigraph for measuring sleep in healthy adults) for recording. Throughout the study, participants will wear an actigraph (Micro Motionlogger SleepWatch®, Ambulatory Monitoring, Inc.; AMI) and report their bedtime, sleep onset latency, and wake time on a daily sleep diary. Alcoholic drinks, caffeinated beverages, prescription, over-the-counter medicines, and other preventive interventions will be prohibited during the trial.

### Provisions for post-trial care {30}

If the condition of a subject worsens after the trial or is accompanied by severe complications or serious adverse reactions, the specialist will take medical measures to deal with the harm based on the subject’s condition. The treatments will be free.

### Outcomes {12}

#### Primary outcome

##### Profile of Mood States Scale

The POMS [36] is a well-validated, 65-item self-report measure comprising six subscales: tension/anxiety, depression/dejection, anger/hostility, energy/activity, fatigue/vigor, and confusion/bewilderment. Participants will report on their mood using a 5-point scale (“not at all” to “extremely”).

#### Secondary outcomes

##### Positive and Negative Affect Schedule Scale

The PANAS [37] will be used to assess the positive and negative effects. Participants will be shown 20 adjectives with 10 describing positive moods and 10 describing negative moods. They will respond using a 5-point Likert scale (1 very slightly, 5 extremely).

##### Noldus FaceReader

The Noldus FaceReader software (FR; version 7.0, Noldus Information Technology) [38] is a facial analysis program that detects emotional facial expressions in film and photographs. The FaceReader can detect six basic emotions, happiness, sadness, anger, fear, surprise, and disgust, as well as neutral states. The FaceReader can also analyze the valence of facial expressions as well as the general state of arousal. The video stimuli are analyzed frame-by-frame to detect the intensity by which each of the six basic emotions is expressed on a scale of 0 to 1, where 0 indicates the absence of emotion while 1 indicates maximum intensity. In this study, the focus will be on the participants’ emotions after sleep deprivation. Prior to analysis, all videos will be calibrated to each participant’s own neutral expression to achieve the most accurate results. The videos will then be analyzed using the batch analysis mode, which sequentially analyzes each video without the need for supervision. Videos of participants’ facial expressions will be recorded using Logitech HDC 920 PRO Webcam, which will be placed above the computer screen. The videos will be processed using the Noldus FaceReader software and Observer XT (version 12.5, Noldus Information Technology). The software’s artificial intelligence is trained to register the activation of 20 action units (AUs) and to indicate scores for happiness, surprise, anger, sadness, disgust, and scared faces as proposed by the basic emotion framework.

### Participant timeline {13}

The trial will comprise 1-week baseline, 1-week preventative treatment, 30-h TSD, and 24-h after waking follow-up periods. During the 30-h TSD period, participants will be assessed every 3 h for a total of 11 sessions. They will be evaluated at 7:00 am (baseline), 10:00 am, 1:00 pm, 4:00 pm, 7:00 pm, 10:00 pm, and on the next day at 1:00 am, 4:00 am, 7:00 am, 10:00 am, and 13:00 pm. AE will also be recorded. Table 2 shows the participant timeline. The SD study participants’ timeline of activities and assessments during hospitalization is shown in Fig. 3.

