### Objectives {7}

This study is designed to evaluate the efficacy and safety of EA for the prevention of negative moods after SD. Moreover, the effects of EA on mood after SD at different time points will be compared. The findings of this trial will provide more reliable evidence for clinical acupuncture prevention in the treatment of negative moods after SD.

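### Four or five of the ten post-baseline sessions fall on an ordinary waking day before the withheld night, yet the analysis treats them like the 30-h session as tests of mood after sleep deprivation

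*Protocol article*

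**What the plan says.** All references are to the protocol article.

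- **Objectives {7}**: "This study is designed to evaluate the efficacy and safety of EA for the prevention of negative moods after SD". The same section adds a comparison of effects at different time points after deprivation. The title speaks of 30 h of total deprivation.
- **Sleep deprivation procedures**: "Sleep deprivation will start at 7:00 am (baseline). Total sleep deprivation will be 30 h".
- **Participant timeline {13}**: "During the 30-h TSD period, participants will be assessed every 3 h for a total of 11 sessions". The times are given as "They will be evaluated at 7:00 am (baseline), 10:00 am, 1:00 pm, 4:00 pm, 7:00 pm, 10:00 pm, and on the next day at 1:00", and the remaining day-2 times are 4:00, 7:00, 10:00 and 13:00.
- **Inclusion criteria**: for the week before the trial, sleep must lie between 21:00 and 09:00 and last at least 7 h per night.
- **Plans for assessment and collection of outcomes {18a}**: one further assessment takes place in the 24-h follow-up after waking.
- **Statistical methods {20a}**: POMS, PANAS and FaceReader "will be compared among the three groups at all time points using ANOVA", with significance at p ≤ 0.05. No session is given a different role. The 7:00 session is called baseline in the timeline, but the analysis section neither exempts it nor uses it as a reference.

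**The concern.** The objective concerns mood once sleep has been lost. With a clock that starts in the morning, the first sessions record how people feel after 3, 6, 9 and 12 h awake, which is an ordinary day. The analysis section gives these sessions the same standing as the one at 30 h.

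The AE and NAE arms reach this day after a week of daily electroacupuncture, while the blank arm has had no treatment. The arms may well differ in everyday mood at 10:00 on day 1 for reasons unrelated to sleep loss. Under the plan, such a difference is a primary-outcome result within the deprivation period and could be presented as prevention of negative mood after deprivation. It would not show that.

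**Working it through.** **Inputs.** Start 7:00, length 30 h (Sleep deprivation procedures); one session every 3 h, 11 sessions (Participant timeline); sleep window 21:00 to 09:00 and at least 7 h of sleep (Inclusion criteria).

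**The plan's own figures.** 30/3 + 1 = 11 sessions, and 7:00 + 30 h = 13:00 on day 2. Both reproduce. Session k (k = 0 to 10) takes place 3k hours after 7:00.

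**Sessions before the withheld night.** The earliest permitted sleep time, 21:00, is 14 h after the start.

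- k = 0 (7:00) is the labelled baseline, which leaves 10 sessions.
- k = 1 to 4 (10:00, 13:00, 16:00, 19:00) are at 3, 6, 9 and 12 h. All are below 14 h, so four sessions precede the night for every permitted bedtime.
- k = 5 (22:00) is at 15 h. It comes 1 h after a 21:00 bedtime, but no later than bedtime for anyone who goes to bed at 22:00 or after.

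The count is therefore 4 of 10 (40%) for a 21:00 bedtime and 5 of 10 (50%) for a bedtime of 22:00 or later. Only one session, k = 10, is at 30 h.

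**Where the boundary is soft.** Hours of the withheld night already missed = session time − usual bedtime, with 0 if negative:

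| Usual bedtime | at 19:00 | at 22:00 | at 1:00 | at 4:00 |
|---|---|---|---|---|
| 21:00 | 0 | 1 | 4 | 7 |
| 22:00 | 0 | 0 | 3 | 6 |
| 24:00 | 0 | 0 | 1 | 4 |
| 02:00 | 0 | 0 | 0 | 2 |

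With a usual wake time of 7:00, the 7-h rule makes 24:00 the latest bedtime (7:00 − 7 h). The criteria themselves allow 02:00 (09:00 − 7 h). For such a sleeper the 1:00 session also precedes the night. Conversely, someone who usually wakes at 09:00 and starts at 7:00 may already have lost up to 2 h at the end of the previous night. Every session from 4:00 on day 2 onward follows some loss for all permitted bedtimes.

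**Set against the analysis.** The objective needs sessions after sleep loss. The analysis section takes all sessions and does not distinguish 10:00 on day 1 from 13:00 on day 2.

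**The case against.** *The schedule is coherent.* Timing total deprivation as hours awake from the morning is internally consistent. This stands: a reader might infer that the 30-h label or the schedule is wrong, and the documents do not support that.

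*Early sessions have a purpose.* A trajectory needs early points, and 7:00, 10:00 and 13:00 on day 1 share clock times with day-2 sessions, so they are natural references. This also stands and is a reason to keep them. It is no reason to let a between-arm difference there count as efficacy after deprivation.

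*Nothing says that one early difference proves prevention.* True; the misreading is possible, not prescribed. But the section sets no session aside, so nothing prevents it.

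*This is only multiplicity.* The number of tests is a separate matter. Early sessions carry no more type I error than late ones, so false-positive rates would not measure this problem. Adjusting for the number of tests would also still leave a 10:00 day-1 result standing as efficacy.

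*An analysis plan that is not shown may settle it.* It may, but the article itself already states the rule of comparing at every time point.

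Three stronger readings are tempting and go too far:

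- That no participant can have lost any sleep on the morning of day 1. This fails for habitual 09:00 wakers.
- That five or six of 11 sessions are misused efficacy points. This counts 7:00, which is labelled baseline.
- That the estimated effect is diluted in proportion to the early sessions. This presupposes a mean over sessions, which the plan never uses, and an effect confined to deprivation-induced mood, which the documents do not establish.

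**Conclusion.** The point holds in a limited form. Four of the ten post-baseline sessions, or five for participants with a bedtime of 22:00 or later, precede the night whose sleep is withheld, yet the analysis gives them the same role as the 30-h session. The objective and the all-sessions comparison do not match.

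The conclusion assumes that 7:00 is roughly the participants' usual wake time. This is inferred from the stated start of deprivation and the sleep criteria, because the schedule table and the hospitalization figure are not shown. The four sessions precede the withheld night under any permitted bedtime. Only the claim that no sleep at all has been lost by then depends on wake time. The data remain usable; what needs limiting is the claim that each session may support.

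**What to change.** Keep every assessment as scheduled. In Participant timeline {13} and Statistical methods {20a}, give the sessions distinct roles:

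- **Primary efficacy time point:** POMS at 13:00 on day 2, the 30-h session that matches the title.
- **Supportive:** the other day-2 sessions (1:00, 4:00, 7:00, 10:00), with a note that 1:00 is borderline for late bedtimes.
- **Descriptive:** day-1 sessions from 10:00 to 22:00, labelled as the trajectory before sleep loss and not used as evidence of prevention after deprivation. A note should say that 22:00 already follows a 21:00 bedtime.
- **Reference:** 7:00 on day 1 as the pre-deprivation value, stating that it follows the week of electroacupuncture and so is not a pre-treatment baseline.
- **Recovery:** the single follow-up assessment in {18a}, reported separately.

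Apply the same roles to PANAS and FaceReader as secondary outcomes.

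The cost is wording in two sections; no visit, participant or data item is added. The Sample size section does not tie its POMS means to a session, so naming 13:00 does not conflict with it. The planned end of recruitment precedes the article's publication date, so the change should be dated and made before the group codes are opened. The downside is that day-1 differences can no longer be claimed as efficacy.
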